## Abstract

**Background:**

Hepatitis C virus (HCV) is a growing public health problem with a large disease burden worldwide. In China many people living with HCV are unaware of their hepatitis status and not connected to care and treatment. Crowdsourcing is a technique that invites the public to create health promotion materials and has been found to increase HIV testing uptake, including in China. This trial aims to evaluate crowdsourcing as a strategy to improve HCV awareness, testing and linkage-to-care in China.

**Methods:**

A randomized controlled, two-armed trial (RCT) is being conducted in Shenzhen with 1006 participants recruited from primary care sectors of The University of Hong Kong-Shenzhen Hospital. Eligible participants are ≥30 years old; a resident in Shenzhen for at least one month after recruitment; no screening for HCV within the past 12 months and not known to have chronic HCV; and, having a WeChat social media account. Allocation is 1:1. Both groups will be administered a baseline and a follow-up survey (4-week post-enrollment). The intervention group will receive crowdsourcing materials to promote HCV testing once a week for two weeks and feedback will be collected thereafter, while the control group will receive no promotional materials. Feedback collected will be judged by a panel and selected to be implemented to improve the intervention continuously.

Those identified positive for HCV antibodies will be referred to gastroenterologists for confirmation and treatment. The primary outcome will be confirmed HCV testing uptake, and secondary outcomes include HCV confirmatory testing and initiation of HCV treatment with follow-ups with specialist providers. Data will be collected on Survey Star^@^ via mobile devices.

**Discussion:**

This will be the first study to evaluate the impact of crowdsourcing to improve viral hepatitis testing and linkage-to-care in the health facilities. This RCT will contribute to the existing literature on interventions to improve viral hepatitis testing in primary care setting, and inform future strategies to improve HCV care training for primary care providers in China.

**Trial registration:**

Chinese Clinical Trial Registry. ChiCTR1900025771. Registered September 7th, 2019, http://www.chictr.org.cn/showprojen.aspx?proj=42788

## Background

Hepatitis C Virus (HCV) is a growing global health problem, with 71 million people estimated living with chronic HCV infection worldwide in 2015 [1]. The global number of deaths due to HCV increased from 333,000 in 1990 to 704,000 in 2013 [2], and it is estimated that HCV-related mortality will triple by 2025 [3]. In China, it is estimated that at least 8.9 million people are living with an identified chronic HCV infection [4]. Notwithstanding, China has the largest burden of liver cancer, accounting to 51% of all global liver cancer death [4]. If untreated, HCV infection can lead to advanced liver diseases, including cirrhosis, liver failure, and hepatocellular carcinoma [5]. In the current era of direct acting antivirals, early testing and treatment can effectively cure HCV and effectively reduce hepatitis-related mortality [6].

Low testing rate and poor linkage to care are key barriers to HCV treatment in China. Since 2018, direct acting antivirals (DAA) regimens such as sofosbuvir/velpatasvir (SOF/VEL) have been included in the national recommended list of essential medications in the China National Formulary (CNF) and have become accessible to patients with a diagnosis. However, only 18% of the HCV-infected population in China had been diagnosed and less than 1.3% actually received treatment [7]. In China, HCV is primarily diagnosed by passive detection, a surveillance system targeting patients seeking care for other illnesses apart from hepatitis, such as enrolled into the hospital for a procedure or surgical intervention, contributing to an underestimation of the actual number of HCV-infected population. Additionally, HCV antibody detection methods and instruments are found to be inconsistent across hospitals. Weakly positive results were considered to be negative, hence, the reported anti-HCV positive rate was slightly lower than the actual level [8]. This may result to an incomplete confirmatory testing since approximately 25–30% of antibody positive will not experience any chronic infection [8].

Promotion of testing and subsequent linkage-to-care service are crucial for effectively curbing the spread of viral hepatitis as well as hepatitis-related morbidity and mortality in China. However, patients are often lost in labyrinth of the Chinese healthcare system and are unable to obtain appropriate screening and treatment. Primary healthcare providers have reported that the lack of motivation and specific training hinder their eagerness to provide HCV testing and treatment to patients, especially in the primary care settings in China [9]. As a result, voluntary HCV testing rates across China are low and HCV services are underutilized despite a huge drop in the pricing of the treatment in the last year.

Crowdsourcing is a form of community engagement which invites the public for brainstorming of ideas and then promotes the solutions with the public audience [10]. It has the potential to expand the role of primary care in promoting viral hepatitis testing and care continuum in China, which will improve healthcare access for the millions of individuals infected with HCV (see Fig. 1). Further, research has shown great beneficial effects by employing crowdsourcing technique in healthcare setting- materials developed through crowdsourcing increased Human Immunodeficiency Virus (HIV) testing uptake and condom use [11, 12]. In addition, social media campaigns that involve active community participation have been associated with higher rates of HIV and sexually transmitted infection (STI) testing compared to passive testing campaigns [13, 14]. Data from 100 Chinese individuals showed that a crowdsourced intervention of images and videos substantially increased HBV testing compared to the standard of care (37.5% HBV testing in the intervention arm, 14.3% testing in the standard of care arm, OR 3.60, 95% CI 1.10–11.74) [15].

**Fig. 1 Fig1:**
[figure not shown]
Crowdsourcing: the “bottom-up” approach to solicit ideas on HCV testing and linkage to care

### Objectives

The current study aims to compare the effects of a crowdsourcing intervention to the control on HCV test uptake among patients attending the primary care departments in a tertiary hospital in China. The hypothesis is that the crowdsourced intervention will be superior to the control in promoting HCV test uptake among patients attending the primary care departments in a tertiary hospital in China.

## Methods

### Study design

This study will include: a pilot study to test the feasibility of participant recruitment in a tertiary hospital in Shenzhen and the social media-based intervention delivered on smartphones; a randomized controlled trial (RCT) to investigate the effectiveness of a crowdsourced intervention compared to no intervention (standard-of-care) in increasing HCV test uptake and linkage-to-care i.e. patients found to be positive for HCV will be referred onto the Division of Gastroenterology of HKU-SZH for further management, if agreeable to the patients.

### Study setting

All phases of this study is conducted through the University of Hong Kong-Shenzhen Hospital (HKU-SZH) in Shenzhen, China. HKU-SZH was established in 2012 as an affiliated hospital of the University of Hong Kong. The hospital has comprehensive clinical services and reported 1.52 million outpatient visits and 65,856 inpatient discharges in 2019. With a “smart hospital” policy in which all appointment bookings, payments, and laboratory results can be processed by each patient’s personal smartphone, HKU-SZH is equipped to implement technology-based interventions.

The city of Shenzhen is located in southern China bordering Hong Kong. Internal migrants from across China are drawn to Shenzhen by the unique economic opportunities of this fast-growing city [16]. A meta-analysis found increased rates of infectious disease, in particular HCV, in Chinese rural-to-urban migrants [17], making Shenzhen a particularly crucial region for increasing viral hepatitis awareness and improving access to care.

We will work primarily with two outpatient departments at HKU-SZH: the Department of Family Medicine and Primary Care (FMPC) and the Division of Gastroenterology under the Department of Medicine. FMPC currently draws 100,000 patient visits per year from the municipality of Shenzhen, Guangdong as well as nearby provinces. The Division of Gastroenterology currently draws about 60,000 outpatient visits and 2500 inpatient discharges per year, including patients with chronic liver disease and viral hepatitis.

### Recruitment

Recruitment will continue until 1006 eligible subjects are enrolled. The primary recruitment sites will be FMPC clinic rooms, as well as the endoscopy suite of HKU-SZH, which performs 22,000 endoscopies per year. Patients will be recruited by physicians during their clinic or endoscopy suite visit. HCV screening at endoscopy suites in the United States has been shown to increase HCV testing uptake by threefold [18]. In China, there is evidence that the reported prevalence of HCV increases with age, and individuals above the age of 30 years have seen an increase in reported incidence from passive HCV detection [19].

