### Randomization and allocation

Once they have signed the consent form, participants will be randomly allocated on a 1:1 ratio to either the intervention or control group through a randomization procedure using permuted blocks. SAS software (Cary, North Carolina, USA) will be used to create the allocation sequence using PROC PLAN and RANUNI functions. Participants will be allocated sequentially in the order in which they are enrolled. This study will be not be blinded, since participants will know their randomization assignment based on whether they receive the intervention, and investigators will be aware of the randomization assignment.

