### Data analysis

#### Primary analysis

Participant baseline characteristics will be summarized using descriptive analyses. The primary analysis will evaluate whether the crowdsourced internet-based intervention package is superior to standard-of-care in increasing HCV testing uptake among the general public and target populations in China. The effect of the intervention on HCV testing uptake will be evaluated first using an intention to treat analysis that includes participants lost to follow-up. The proportion of participants with confirmed HCV testing in the intervention and control arms will be calculated separately using a 95% binomial proportion confidence interval (CI). The proportion of testing uptake between intervention and control arms will be compared using chi square test. Logistic regression adjusted with potential confounders will be applied to confirm the effect of intervention on the outcomes. Moreover, multiple logistic regression will be conducted to evaluate the effect of the following baseline factors on HCV testing uptake: previous health care service utilization behavior; trust in physicians and the health care system; knowledge of and access to healthcare services; membership in groups at high risk for HCV.

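### The question is posed for primary care patients, but the sample also includes endoscopy patients, and an unstratified pooled test is read as applying to the general public

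*Protocol article*

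**What the plan says.** The protocol article describes the study population in three ways.

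- **Primary care patients.** The Methods paragraph of the Abstract says the trial has "1006 participants recruited from primary care sectors of The University of Hong Kong-Shenzhen Hospital". The Objectives state both the aim and the superiority hypothesis for HCV test uptake "among patients attending the primary care departments in a tertiary hospital in China".
- **Primary care and endoscopy patients.** The Recruitment section says "The primary recruitment sites will be FMPC clinic rooms, as well as the endoscopy suite of HKU-SZH" and adds that "Patients will be recruited by physicians during their clinic or endoscopy suite visit". It puts the suite's volume at 22,000 endoscopies a year. The Study setting section names Family Medicine and Primary Care (FMPC) and the Division of Gastroenterology as two separate outpatient departments, with 100,000 visits a year at FMPC. No cap or target share is given for endoscopy recruits.
- **The public at large.** The Primary analysis section says the trial will judge superiority "among the general public and target populations in China".

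Allocation is 1:1 by "a randomization procedure using permuted blocks", in order of enrolment, with no stratification factor named. The primary comparison is a chi-square test of the two proportions, followed by logistic regression adjusted for potential confounders that are not listed. Under Outcomes, any anti-HCV test confirmed by medical records within 4 weeks of enrolment counts, whatever prompted it.

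**The concern.** A reader who takes the Objectives at face value will read the final risk difference as the effect in primary care. It will be an average over primary care and endoscopy patients, with weights set by whoever happens to be enrolled. If uptake or response to the messages differs between the two settings, the pooled figure describes neither. The Primary analysis wording then extends that figure to a population from which nobody was sampled.

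Two lesser matters follow.

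- If the underlying testing rate differs by site, a test that ignores site gives up some precision.
- The Background says HCV in China is found mainly by passive detection in people seeking other care, "such as enrolled into the hospital for a procedure or surgical intervention". If endoscopy recruits are tested for such reasons after enrolment, those tests count as uptake in both arms and reduce the difference.

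**Working it through.** **1. The plan's own figure.** Inputs from Sample size: 35% v 45%, 90% power, alpha 5%. I take alpha as two-sided, which reproduces the stated number.

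n per arm = [1.960·√(2·0.40·0.60) + 1.282·√(0.35·0.65 + 0.45·0.55)]² / 0.10² = (1.358 + 0.883)² / 0.01 = 502.3, so 503 per arm and 1006 in total. Power at 503 per arm is 90.0%. The calculation treats all 1006 as one population.

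**2. Power for the question as the Objectives pose it.** Let f be the share of recruits from endoscopy. The article does not give f, so these values are assumptions. At 35% v 45%, power in the FMPC stratum is Φ[(0.10·√n − 1.358)/0.689], with n = 503·(1 − f) per arm.

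| f | FMPC patients per arm | Power |
|---|---|---|
| 0 | 503 | 90% |
| 25% | 377 | 80% |
| 50% | 251 | 63% |

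**3. Conditional dilution.** Let t be the share of endoscopy recruits who would be tested for procedural reasons in either arm. The article does not give t either. With q = f·t, each arm's rate becomes p(1 − q) + q, and the difference becomes 0.10·(1 − q).

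One rough guide to f is the ratio of the stated volumes: 22,000/(100,000 + 22,000) = 18%. This assumes that recruitment is proportional to volume.

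| f | t | q | Control | Intervention | Difference (points) | Power, 503 per arm |
|---|---|---|---|---|---|---|
| any | 0 | 0 | 35.0% | 45.0% | 10.0 | 90% |
| 18% | 10% | 1.8% | 36.2% | 46.0% | 9.8 | 89% |
| 18% | 20% | 3.6% | 37.3% | 47.0% | 9.6 | 87% |
| 25% | 50% | 12.5% | 43.1% | 51.9% | 8.75 | 79% |

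**4. What stratifying by site would change.** At f = 25% and t = 50%, the FMPC rates are 35% v 45%. The endoscopy rates are 0.5 + 0.5·0.35 = 67.5% v 0.5 + 0.5·0.45 = 72.5%.

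- The weighted difference is 0.75·10 + 0.25·5 = 8.75 points, the same as without strata.
- The within-site variance term is 0.75·(2·0.40·0.60) + 0.25·(2·0.70·0.30) = 0.465. Pooled, it is 2·0.475·0.525 = 0.499.
- Power rises from 79% to 82%.

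Stratification therefore recovers some precision but does not restore the lost 1.25 points.

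**The case against.** **Recruiting at both sites is deliberate.** The article names its two working departments openly, and the Discussion acknowledges that hospital-based recruitment and the need for a smartphone and social media limit reach. That is fair as to intent. It does not make the Abstract and Objectives agree with Recruitment, and it sits badly with the wider claim in the Primary analysis section.

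**Strata and covariates may be in the full protocol or analysis plan.** This stands for the allocation lists, whose silence on site is no finding. The adjusted logistic regression could also include site. The primary test itself, however, is stated, and it is an unstratified chi-square.

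**Lack of site strata causes no bias.** This also stands. One-to-one randomization of 503 per arm is balanced by site in expectation. The chance standard deviation of the between-arm difference in endoscopy share is √(2f(1 − f)/503), or 2.4 points at f = 18% and 2.7 points at f = 25%.

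**A stronger reading is tempting but not supported.** A reader might infer that routine tests around endoscopy seriously dilute the effect, and that the missing stratification is the cause. The documents do not support either step.

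- The Background passage describes national case-finding. Nothing says that endoscopy patients at this hospital are routinely tested for anti-HCV.
- Recruitment takes place at the visit itself, so a test done before that visit falls before enrolment. A self-reported anti-HCV test in the past 12 months is an exclusion. What remains is testing after enrolment, and the exclusion depends on self-report.
- Procedural tests would occur in both arms with or without strata.
- Severe losses of power appear only if high values of f and t are assumed.

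**Conclusion.** The mismatch of populations is certain from the text. The question is put for primary care patients, the sample adds endoscopy patients in an unstated proportion, and the conclusion is worded for the general public. As planned, the pooled chi-square does not directly answer the stated question.

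The size depends on the endoscopy share. For the primary care patients alone, power at 35% v 45% would be about 80% if that share is 25% and 63% if it is 50%; both shares are assumed.

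Dilution by procedural testing is a conditional risk only. Power would be 87–89% under f = 18% and t = 10–20%, and 79% under f = 25% and t = 50%, with every f and t assumed. If no such tests occur, power stays at 90%. The stated sample size is arithmetically correct. The point is worth acting on because the remedy costs almost nothing and makes the result interpretable.

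**What to change.** 1. **Reconcile the population wording** in the Abstract, Objectives, Recruitment and Primary analysis sections so that the population named is the one recruited: WeChat-using patients aged 30 or over at the FMPC clinics and endoscopy suite of HKU-SZH. Drop the claim about the general public.
2. **Stratify the primary comparison by recruitment site**, using a Mantel-Haenszel risk difference or logistic regression with site as a covariate. Name one of these in advance.
3. **Report the effect by site**, with confidence intervals, and rest any statement about primary care on the FMPC estimate.
4. **Optional:** add a sensitivity analysis that does not count tests recorded as ordered for a procedure. The trial is open-label and the reason for a test is judged after randomization, so the classification rule should be fixed beforehand and, if possible, applied without knowledge of arm.

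The cost is recording the recruitment site for each participant and slightly more analysis. The FMPC estimate will have less power than the pooled one, as shown above, and the report should say so. Items 1 to 3 can be adopted even if enrolment has begun, because none requires a change to the allocation.

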### Eligibility criteria

Prior to enrollment, potential participants must first complete an informed consent form in Chinese language, which explains the purpose of the study as well as the rights and responsibilities of the subject participants. Participants are invited to participate if they are 30 years old or older, have Chinese nationality, and will reside in Shenzhen for the following month. Participants will be excluded if they self-report one of the followings: known chronic HCV infection, testing for serum anti-HCV in the past 12 months, current or planned pregnancy, currently undergoing complex medical treatment for other conditions. All eligible participants must provide a working unique mobile phone number and a WeChat account to be enrolled. Wechat is currently the most popular messaging social media app in China, with more than 1 billion active users and 45 billion daily text messages according to the statistics shown in [20].

### Sample size

The anti-HCV seroprevalence in China is estimated to be between 2.2 to 3.7%, giving an average of 3% prevalence of anti-HCV in the recruited population [21, 22]. The testing rate of conventional public health marketing methods (messages created by public health professionals) is approximately 35% [14]. If we conservatively assume crowdsourcing improves testing rates by 10%, together with 90% power and an alpha risk of 5%, a sample size of 1006 patients (*n* = 503 in each arm) will be required.

### Randomization and allocation

Once they have signed the consent form, participants will be randomly allocated on a 1:1 ratio to either the intervention or control group through a randomization procedure using permuted blocks. SAS software (Cary, North Carolina, USA) will be used to create the allocation sequence using PROC PLAN and RANUNI functions. Participants will be allocated sequentially in the order in which they are enrolled. This study will be not be blinded, since participants will know their randomization assignment based on whether they receive the intervention, and investigators will be aware of the randomization assignment.

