### Intervention

The crowdsourcing intervention is composed of two parts: 1) promotional materials developed through a nation-wide open contest in China, 2) a series of mini crowdsourcing contests to solicit participant feedback to improve the promotional materials. The impact of crowdsourcing is expected through both receiving the crowdsourced messages and actively engaging with the message.

Upon enrollment, participants will be required to add the designated study account as a WeChat contact. The study account will be monitored and maintained by the researchers. The intervention materials—two videos and two images designed to increase awareness about HCV—will be delivered to participants over the course of 2 weeks as individual messages. The initial materials were developed through a nation-wide open contest in China, and was previously evaluated for hepatitis testing uptake in men-who-have-sex-with-men (MSM) in China [15].

Next, participants will be asked whether they have expertise in the following fields: healthcare, social media, or education. Participants who have expertise will be asked to reflect on the intervention based on their expertise, while participants without expertise will be encouraged to reflect based on personal experience. All participants will be invited to submit 50- to 200-character suggestion on how to improve the intervention materials. Submissions will be judged by a panel of health workers, researchers, and community advocates on the following: [1] potential to encourage HCV testing [2]; creativity [3]; potential to engage social media users; and [4] feasibility in clinical settings in Shenzhen. Suggestions for improvement will be shared anonymously among agreeable participants who are receptive to receive frequent updates from WeChat. Top scoring suggestions that meet the predesignated standard will receive cash prizes up to 500 Chinese yuan (72.5 USD). Feasible suggestions will be incorporated into the intervention materials and presented to the next round of participants.

Participants in the control arm will only receive the baseline and follow-up surveys via WeChat. They will not receive any promotional materials as there are currently no materials used in standard-of-care HCV testing promotion at the hospital. In the final week of the intervention period, all participants will receive a reminder to obtain HCV testing and a follow-up survey.

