### Outcomes

The primary outcome is the number of anti-HCV screening tests completed by participants in either RCT arm within 4 weeks after enrollment. This dichotomous outcome will be determined by a single endpoint: uptake of HCV antibody screening test. Participants will only be counted as achieving the primary outcome if medical records at HKU-SZH or in another facility in Shenzhen confirm that they had tested for HCV during the intervention period. Medical records would be assessed based on either the administrative record or photo verification of official testing record.

Secondary outcomes are as follows: rate of participation in the crowdsourcing intervention; content of feedback submissions; number of participants that self-report HCV antibody testing but are not confirmed by medical records; number of participants that follow-up for HCV confirmatory testing; number of HCV diagnosed participants to continue with anti-HCV treatment, versus those who decline treatment for any reason; number of participants that will be completely cured of HCV infection, versus number that drop out prior to completing treatment; number of participants diagnosed with chronic liver disease (including cirrhosis, liver failure, or hepatocellular carcinoma); number of participants that will return to primary care for chronic liver disease follow-up or future screening of HCV and other conditions. Definitions for all study outcomes are provided in Table 1.

**Table 1 Tab1:** Primary and secondary outcomes with definitions

**Primary Outcome**	**Definition**
Confirmed HCV testing uptake	Participants that complete HCV testing as confirmed by medical records at HKU-SZH or other public facility in Shenzhen within 4 weeks of enrollment
**Secondary Outcomes**	**Definitions**
Self-reported HCV testing uptake	Participants that complete HCV testing within 4 weeks of enrollment, self-reported in follow-up survey
Followed-up for HCV confirmatory testing	Participants that follow-up with a provider at HKU-SZH for HCV RNA diagnostic testing, as confirmed by medical records at HKU-SZH or other public facility in Shenzhen
Self-reported follow-up for HCV confirmatory testing	Participants that follow-up with a provider at HKU-SZH or other care facilities in China for HCV RNA confirmatory testing, self-reported in follow-up survey

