### Confidentiality

Baseline and follow-up survey data will be collected on Survey Star^@^. For follow-up on HCV testing results at HKU-SZH or in one of the connected public hospitals in Shenzhen, patient records in the electronic medical system will be traced by the research team using self-reported hospital registration ID and demographic information. All study data will be encrypted prior to transmission and will be stored in a secure server and can be access by login information known only to the research team. Ethics approval is obtained through the IRB of HKU-SZH (hkuszh201888).

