### Monitoring

A researcher will check each survey for completion and internal consistency. Each participant’s baseline and follow-up survey and test report will be checked for consistency of their verified cell phone number and demographic information. Test results must be confirmed by testing records at HKU-SZH or verified based on participant socio-demographics as reported in their baseline survey. A telephone number and WeChat account managed by the research team will be made available to participants for any questions or concerns that may come up during the study.

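### All investigators know the arm, including those who confirm the primary outcome, and the reason given for not blinding does not cover outcome confirmation

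*Protocol article*

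**What the plan says.** All references are to the protocol article.

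- **Randomization and allocation.** The trial is not blinded, since "participants will know their randomization assignment based on whether they receive the intervention, and investigators will be aware of the randomization assignment". Allocation follows consent: "Once they have signed the consent form, participants will be randomly allocated on a 1:1 ratio to either the intervention or control group".
- **Intervention.** The materials "will be delivered to participants over the course of 2 weeks as individual messages". On the sending account: "The study account will be monitored and maintained by the researchers". A panel that includes researchers judges participants' suggestions for improving the materials.
- **Outcomes.** The primary outcome is an HCV antibody test within 4 weeks of enrolment, counted only if medical records confirm it. On the evidence: "Medical records would be assessed based on either the administrative record or photo verification of official testing record". One secondary outcome counts participants who report a test that records do not confirm.
- **Confidentiality.** For results at the trial hospital or connected public hospitals, "patient records in the electronic medical system will be traced by the research team using self-reported hospital registration ID and demographic information".
- **Monitoring.** "Test results must be confirmed by testing records at HKU-SZH or verified based on participant socio-demographics as reported in their baseline survey". Phone number and demographics are checked for consistency for each participant.
- **Incentives and compensation.** In either arm, the test is reimbursed only after the research team has confirmed the record, the demographics match, and the test date falls in the intervention period.
- **Recruitment.** "Patients will be recruited by physicians during their clinic or endoscopy suite visit".

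No section describes a person who confirms tests without knowing the arm.

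**The concern.** A laboratory test is an objective event, but it becomes a primary-outcome success only after someone on the research team finds the record, accepts a photo of it, or decides that the demographics on it match the participant. The plan itself expects some claimed tests to fail this step, because it counts them as a secondary outcome.

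People who know the arm could search harder, chase a missing photo longer, or accept an imperfect match more readily in one arm. Such a difference would enter the comparison as if it were uptake. Neither the chi-square test nor the adjusted logistic regression in the Data analysis section could separate it from the effect of the messages.

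Participants cannot be blinded to messages they receive, so confirming the outcome without knowledge of the arm is a main safeguard still available for this endpoint. The article gives it up without a reason that applies to it.

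**Working it through.** **1. Who needs the arm**

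| Task | Section | Must know the arm? |
|---|---|---|
| Sending materials from the study account | Intervention | Yes, the materials go to one arm only |
| Handling the feedback contest | Intervention | Yes, the submissions concern those materials |
| Tracing records by hospital ID and demographics | Confidentiality | No |
| Checking photos of testing records | Outcomes | No |
| Matching demographics and date | Monitoring; Incentives and compensation | No |
| Recruiting at the visit | Recruitment | No role in delivery is described |

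The blanket statement on investigators is therefore wider than the tasks require, but it cannot be dropped for everyone.

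**2. The plan's own figure**

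Inputs from the Sample size section: 35% against 45% (10% read as percentage points), 90% power, alpha 5%, 503 per arm. With a two-sided test and pooled variance under the null:

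n = [1.960 × √(2 × 0.40 × 0.60) + 1.2816 × √(0.35 × 0.65 + 0.45 × 0.55)]² / 0.10² = (1.358 + 0.883)² / 0.01 ≈ 502.3, rounded up to 503 per arm, 1006 in total.

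This reproduces the stated figure, so nothing in the sample size is in question here.

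**3. Effect of unequal confirmation**

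Assume no true effect, p0 = 35% in both arms, and an artificial excess b of confirmed tests in the intervention arm. The documents give no figure for b, so it is an assumption. The 35% is itself the plan's figure for conventional marketing messages. With p1 = p0 + b and p̄ the mean of the two:

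- se0 = √(2 p̄(1 − p̄)/503)
- se1 = √([p0(1 − p0) + p1(1 − p1)]/503)
- P(reject) = 1 − Φ((1.960 se0 − b)/se1) + Φ((−1.960 se0 − b)/se1)

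For b = 0.03: se0 = 0.03036 and se1 = 0.03034. The upper tail is 1 − Φ(0.972) = 0.1655, the lower tail is 0.0016, and the total is 0.167.

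| b (points) | People of 503 | P(reject) |
|---|---|---|
| 0 | 0 | 5% |
| 1 | about 5 | 6.3% |
| 2 | about 10 | 10.1% |
| 3 | about 15 | 16.7% |

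With a base rate of 14.3%, the standard-of-care figure that the Background quotes for HBV testing, the same excesses give 7.3%, 14.3% and 25.6%.

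**4. How large could b plausibly be?**

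For photo records alone, the shift is uptake × share of tests verified by photo × difference in acceptance between arms. Assume a share of 10% to 50% and a difference of 5 to 20 points, neither of which is in the documents.

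- At 35% uptake: from 0.35 × 0.10 × 0.05 = 0.2 points to 0.35 × 0.50 × 0.20 = 3.5 points.
- At 14.3% uptake: from 0.1 to 1.4 points.

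An excess of 1 to 3 points thus lies in the middle and upper part of this range at 35%. At 14.3% the photo route alone does not reach 2 points. Uneven search effort is not covered by this product and cannot be bounded from the text.

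For scale, with 176 of 503 confirmed in the control arm, about 31 extra events (6.2 points) would be needed for significance on their own.

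**The case against.** **The endpoint leaves little room for judgement.** A dated test either exists or does not, medical records must confirm it, and the identity and date checks are the same in both arms. This largely stands. It leaves discretion mainly in photo records, demographic matching and search effort. Equal acceptance rules do not secure equal effort in applying them, and the article does not say how close a demographic match must be.

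**Some investigators must know the arm.** This stands: those who send the materials and handle submissions cannot be kept unaware. It limits the point to confirmation and does not remove it.

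**The figures rest on an assumed excess, all in one arm.** This also stands. They show sensitivity and do not estimate a bias in this trial.

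**Stronger readings that the text does not support.** A reader might infer that recruiting physicians know the arm and prompt testing selectively. The article does not say that they are investigators, learn the allocation or order the antibody test, and allocation comes after consent. Excesses well above those tabulated would need a route of that kind, so they are not used here. A reader might also infer that recruiters could predict assignments from the permuted blocks. That assumes they see past allocations, which is not stated. It would also concern selection at enrolment, not confirmation of outcomes, and an article commonly leaves concealment details to the full protocol.

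**Conclusion.** The point holds for outcome confirmation. The article leaves every investigator aware of the arm, gives a reason that does not cover the staff who confirm tests, and assigns sending and confirming to the same undivided research team. The resulting bias is possible and not shown to occur, and no stated number is wrong. If confirmation differed by 1 to 3 points with no true effect and 35% uptake in both arms, the false-positive rate would rise from 5% to between about 6% and 17%. That rests on the assumed excess, the plan's 35%, and a normal approximation with 503 per arm. This is a low-cost improvement to the protection of the primary endpoint, not a flaw that invalidates the design.

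**What to change.** In the Randomization and allocation section, replace the blanket statement about investigators with text to this effect:

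- Only the staff who operate the WeChat study account and handle the feedback contest know the arm.
- Other existing members of the research team trace and confirm test records from a list without arm, using the same matching rule for every participant.
- The outcome file is locked before arm is merged.
- The allocation is not passed to recruiting physicians, who have no described role in delivering the intervention.

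Describe the trial as open to participants and message senders, with masked outcome verification, and make the Outcomes, Confidentiality and Monitoring sections consistent with this.

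**Cost.** Duties must be split within the team, with access control on the allocation list, an arm-free working list and a file-lock step. The sample size stays at 1006. Masking may be incomplete if participants reveal their arm to those who confirm records.
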